### Primary Objectives

1. Reduce measures of obesity including body mass index (BMI), waist, hip, and neck circumferences, and total skinfold thickness.

2. Reduce systolic and diastolic blood pressure.

3. Improve aerobic fitness profiles and increase PA behaviour.

4. Improve blood lipid profiles and lower levels of plasma inflammatory markers.

5. To assess the impact of motivation to exercise on physiological and psychological outcomes following the cross-curricular intervention

6. To influence psychological well being (mood and negative affect), self concept, and cognitive performance in an intervention group compared with a control.

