### Data Analysis

A quasi-experimental design will be used to compare differences in measured outcomes between pupils assigned to an intervention or control group. Initially, baseline data will be used to perform pearson's product moment correlation coefficients, followed by multiple regression analysis to estimate the significance of selected predictors on CVD risk factors. Dependant t-tests will be employed to assess differences between measures taken at baseline and post-intervention with independent t-tests utilised to detect differences in variables between groups. Statistical significance will be set at *P *≤ 0.05. Power calculations revealed that 100 participants from the exercise group and 60 participants from the control were required to achieve 80% power.

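### Six co-equal primary objectives span about 21–28 outcomes, all tested at P ≤ 0.05, with no lead outcome and a power figure tied to none

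*Protocol article*

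**What the plan says.** The article's Primary Objectives section lists six objectives and does not rank them. Objectives 1 to 3 concern obesity (five measures), systolic and diastolic pressure, and fitness with activity behaviour. Objective 4 is to "Improve blood lipid profiles and lower levels of plasma inflammatory markers". Objective 5 concerns the effect of motivation on the other outcomes. Objective 6 is "To influence psychological well being (mood and negative affect), self concept, and cognitive performance in an intervention group compared with a control".

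The Data Analysis section sets out two kinds of test. For change over time it says: "Dependant t-tests will be employed to assess differences between measures taken at baseline and post-intervention". For the comparison of intervention with control it plans "independent t-tests utilised to detect differences in variables between groups". It continues: "Statistical significance will be set at" P ≤ 0.05. On sample size it states only that "100 participants from the exercise group and 60 participants from the control were required to achieve 80% power". It does not attach that figure to an outcome, an effect size or a standard deviation, and it does not say whether the test is one- or two-sided. The article also does not say which outcome leads or which of the two kinds of t-test decides whether an objective is met.

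**The concern.** With six objectives of equal rank and more than 20 measures beneath them, a reader of the results cannot tell in advance which comparison the trial stands or falls on. Each measure meets the same unadjusted threshold, so one significant result anywhere in the list could be presented as success on a primary objective. The article's Discussion looks ahead to a cost-effective, long-term school strategy, so a chance finding could carry weight. The power figure does not help, because 80% power has meaning only for a named outcome and effect.

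**Working it through.** **1. The plan's own figure.** The 100/60 sample size at 80% power cannot be reproduced without an effect size, standard deviation or sidedness. It can only be back-solved as a standardised effect, using the normal approximation:

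- d = (z for alpha + z for 0.80) × √(1/100 + 1/60), where the square root is 0.1633.
- Two-sided 0.05: (1.960 + 0.842) × 0.1633 = 0.457.
- One-sided 0.05: (1.645 + 0.842) × 0.1633 = 0.406.

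**2. Counting outcomes.** The measures come from Primary Objectives, Blood Sampling and Analysis, Motivation, and Psychological Well-being.

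- *One score per instrument, motivation treated only as an explanatory variable:* obesity 5, blood pressure 2, shuttle run and activity questionnaire 2, lipids and inflammatory markers 8, anxiety, depression, self-perception and attention 4. Total 5+2+2+8+4 = 21.
- *State and trait anxiety and the six named self-perception domains counted separately:* 5+2+2+8+10 = 27.
- *Every listed measure, one score per instrument, with insulin, glucose and all six motivation instruments:* 5+2+2+10+6+3 = 28.

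The range is approximate. Adding insulin and glucose to the 27 would give 29.

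**3. Chance of a false result, independent tests.** Take one two-sided between-group test per outcome at 0.05, with no true effects. For k outcomes the chance of at least one significant difference in either direction is 1 − 0.95^k. In the favourable direction only, it is 1 − 0.975^k.

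| k | Either direction | Benefit only | Expected false positives (0.05k) |
|---|---|---|---|
| 1 | 5% | 2.5% | 0.05 |
| 21 | 65.9% | 41.2% | 1.05 |
| 27 | 75.0% | 49.5% | 1.35 |
| 28 | 76.2% | 50.8% | 1.40 |

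The either-direction chance passes one half at k = 14. The benefit-only chance does so at k = 28.

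**4. Allowing for correlation.** The article gives no correlations, so these are assumptions. With a common correlation ρ between test statistics, the chance is 1 − ∫ φ(u) [p(u)]^k du, where p(u) is the probability that one test is not significant given a shared factor u. For either direction, p(u) = Φ((1.96 − √ρ u)/√(1−ρ)) − Φ((−1.96 − √ρ u)/√(1−ρ)). For benefit only, the second term is dropped.

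| k | ρ | Either direction | Benefit only |
|---|---|---|---|
| 21 | 0.3 | 55.5% | 28.8% |
| 21 | 0.5 | 42.9% | 21.6% |
| 27 | 0.3 | 63.0% | 33.1% |
| 27 | 0.5 | 48.3% | 24.3% |
| 28 | 0.3 | 64.1% | 33.8% |
| 28 | 0.5 | 49.1% | 24.7% |

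A simulation with assumed block correlations (0.8 within obesity, 0.6 within blood pressure, 0.3 within fitness and activity and within blood markers, 0.4 within psychology, 0.1 between blocks) gives 57% and 32% for k = 21, and 65% and 37% for k = 27.

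**5. What a full correction would cost.** If the power figure was computed two-sided at 0.05, so that d = 0.457, Bonferroni adjustment has these effects:

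| Tests | Alpha per test | Power at 100/60 | Pupils for 80% power |
|---|---|---|---|
| 6 | 0.0083 | 56% | 155 + 93 |
| 21 | 0.0024 | 41% | 194 + 116 |
| 27 | 0.00185 | 38% | 200 + 120 |

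One named outcome at 0.05 leaves the stated sample size as it is.

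**The case against.** The strongest defence is that this is a journal article and that an adjustment rule could sit in a statistical analysis plan that is not shown. That stands as far as the missing correction method goes, which is no finding by itself. It does not reach what the article does fix: six undifferentiated primary objectives, one threshold, and a power claim without an outcome. A later correction across all outcomes would also be hard to square with 80% power, as step 5 shows.

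Several stronger readings are tempting, and the article does not support them.

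- *That at least 27 outcomes are primary.* This splits the anxiety inventory in two and self-perception into six. Objective 6 names only mood and negative affect, self-concept and cognitive performance, and the Motivation section, which contains the self-perception measure, presents its scales as causal and moderating variables. One score per instrument gives 21.
- *That a false benefit is more likely than not.* The 75% for 27 independent tests covers both directions. For benefit alone it is 49.5%, and positive correlation lowers it to about 33% at 0.3. Even the either-direction figure falls below one half at a correlation of 0.5.
- *That the plan claims a 5% level it does not have.* The article sets a per-test threshold and makes no claim about the whole family of tests. Nor does it say that success on any one outcome makes the trial positive.
- *That 81 tests will be run (27 outcomes, three tests each).* The article describes two kinds of t-test but does not say that every score gets all of them. If a favourable pre-to-post change in the intervention group also counted as benefit, the chance of a false benefit would be about 70% for 27 independent outcomes, but the article does not state that rule.

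**Conclusion.** The point holds in a limited form. The article gives equal primary status to objectives spanning roughly 21 to 28 outcomes, tests them all at an unadjusted 0.05, and ties its power figure to none of them. It therefore leaves open which result counts as the trial's answer.

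Under the assumption of no effect on any outcome, with one two-sided between-group test each, a spurious difference in some direction has a chance of about 66–76% if the tests are independent and 43–64% at common correlations of 0.3–0.5. A spurious benefit has a chance of about 41–51% and 22–34% respectively. Even the lowest of these is more than eight times the 2.5% of a single two-sided test (21.6/2.5 = 8.6). The exact size depends on the outcome count, on correlations that the article does not give, and on reading its tests as two-sided.

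**What to change.** Name one primary outcome. State that it is decided by the between-group comparison at 0.05, and attach the 100/60 power statement to it with its effect size and standard deviation. The choice of outcome is the sponsor's. If the existing power calculation was made for one of the listed measures, that measure is the natural candidate.

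Relabel all other outcomes as secondary, including fitness and activity if neither is chosen. Then either report them as exploratory, with estimates and confidence intervals, or apply Holm or false-discovery-rate control within stated domains. Every outcome needs a domain: a list of obesity, blood pressure, lipids, inflammation and psychology alone would leave out the shuttle run, the activity questionnaire, insulin and glucose. The text should also say that control within domains does not control error across them. For example, six independent domains each held at 5% still allow up to 1 − 0.95^6 = 26% overall.

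The change costs a few sentences. It needs no extra pupils, provided that the 100/60 calculation holds for the outcome chosen. The downside is that the sponsor must commit to one lead outcome, and fewer secondary outcomes will reach nominal significance if they are adjusted.

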### Intervention

In addition to regular PE lessons (60 min duration), this intervention will aim to increase PA by an additional two hours per week, for 18 weeks. A cross-curricular PA intervention involving all academic subjects termed the 'Activity Knowledge Circuit' will be followed by year eight pupils. These participants will complete 3,200 m of brisk walking during a 60 mins subject (normally classroom based) lesson, where a metronome set at 130 beats per minute will provide a walking speed. Initial pilot work carried out suggests that walking at this intensity for 3,200 m elicits relative oxygen uptake values of 17.0 ± 1.3 ml^-1^kg^-1^min^-1^. Following 18-weeks, performing two intervention lessons per week, it is calculated that energy expenditure will equate to 4039 ± 1387 kcal, leading to a predicted weight loss of 1.2 ± 0.4 lbs, without accounting for confounding variables.

Each intervention lesson will be supervised by a subject teacher, and researcher or member of the PE department to ensure participants walk at the correct speed. Each participant will perform two intervention lessons per week, in addition to two regular PE lessons, thereby increasing activity by two hours a week. Intervention lessons will be integrated into the regular school timetable, and no more than four intervention lessons will be delivered by each curriculum subject during the 18-week period. Short tasks, in line with current curriculum, will be provided by subject teachers for participants to complete at stations set every 400 or 800 m. Participants will therefore, still follow national curriculum whilst exercising at the same time. Tasks are to be designed by teachers to last no longer than 60 seconds at each station. Physical Education lessons are to be implemented as usual.

Normally, all intervention classes will be performed outside on school premises on a pre-determined course. In adverse weather conditions, a course of equal distance has been arranged undercover, again on school premises, so preventing any disruption to the intervention schedule. Participants will wear school uniform whilst taking part, but suitable footwear will be advised. Registers are to be kept during each intervention-led lesson to monitor absentees.

### Measurements

All measurements will be performed pre- and post-intervention for both intervention and control groups (Figure 1). These are to be carried out by trained, gender specific individuals during PE lessons and on school premises to ensure minimal disruption to the curriculum. Individuals performing measurements will be CRB checked prior to data collection. Pre- and post-intervention measurements will be voluntary and last no longer than three weeks. Participants will be informed that they may withdraw at any point and that all information collected would be confidential.

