## Background

Cardiovascular disease (CVD) is the leading cause of mortality worldwide [1]. In 2005 there was a reported 17.5 million deaths related to the disease, representing 30% of the global population [2]. Risk factors for CVD including obesity, blood pressure, blood lipids and lipoproteins have shown to track from childhood through to adulthood [3,4]. Metabolic syndrome (MetS) is the co-existence of multiple risk factors including hyperinsulinaemia, glucose intolerance, hypertension, decreased levels of high-density lipoprotein cholesterol (HDL-C) and elevated triglycerides (TG) [5]. At least one MetS risk factor was evident in one third of children (12-19 years) from the Third National Health and Nutritional Survey [6]; whereas one in ten was diagnosed with the syndrome itself when using the National Cholesterol Education Programme - Third Adult Treatment Panel definition. The prevalence of overweight and obesity for children (4-18 years) in the UK is reported to be 15 and 4% respectively [7]. Furthermore, in comparison to England (2.9%) obesity was more prevalent for those living in Scotland (7.6%) and Wales (6.5%).

For many, overweight and obesity is the result of the combined effect of excess energy consumption and inadequate physical activity (PA) [8]. Previously, for children and adolescents PA has correlated negatively with body fatness and insulin resistance [9-11]. Conclusions regarding associations with blood lipids and lipoproteins are less clear. Although a recent meta-analysis reported no effect of aerobic exercise on non-high-density lipoprotein cholesterol, further studies are warranted [12]. Despite this, significant inverse relationships between PA and metabolic risk scores have recently been reported [13,14], highlighting the importance of PA on childhood health. Schools are thought to be the ideal setting to implement PA interventions to combat CVD risk factors, with access to large populations from a variety of social classes, coinciding with a monitoring structure already in place [15,16].

The association between psychosocial variables and obesity is complex. Research findings in this area indicate that there is a relationship between depression in youth and subsequent obesity [17,18]. The stigma attached to being overweight may affect peer relationships and may result in children and adolescents feeling less able to participate in PA and more likely to suffer from psychological distress [19,20].

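### Measurement is voluntary and the planned t-tests are unadjusted, so selective refusal of the post-test could bias a comparison of post values; a group-by-time model using every baseline would be safer

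*Protocol article*

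**What the plan says.** Protocol article, Measurements: "Pre- and post-intervention measurements will be voluntary and last no longer than three weeks". The same paragraph adds: "Participants will be informed that they may withdraw at any point". No uptake or attrition rate is given.

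Protocol article, Data Analysis: "Dependant t-tests will be employed to assess differences between measures taken at baseline and post-intervention", and "independent t-tests utilised to detect differences in variables between groups". The article does not say whether the second test compares post values or changes, and it names no baseline adjustment for the group comparison. On size it says: "100 participants from the exercise group and 60 participants from the control were required to achieve 80% power". It gives no outcome, effect size, SD or dropout allowance for that calculation.

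Allocation is by school year and not randomised (Participants; Discussion). The only predicted effect in the article is a weight loss of 1.2 lb, derived from energy expenditure (Intervention). It is not linked to the sample size.

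**The concern.** The measurements include skinfolds, a shuttle run in the sports hall and fasting venous blood. A child can decline any post-test, and the children who decline may not be typical. The Background says that the stigma of overweight "may result in children and adolescents feeling less able to participate in PA and more likely to suffer from psychological distress". That sentence concerns taking part in activity, not being measured, but it makes refusal related to weight or fitness plausible.

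The two named tests respond to refusal differently. A paired t-test needs both values. An independent t-test on post values uses whoever supplies a post value and ignores the baselines already collected. If heavier or less fit children leave one group more than the other, that group's post mean moves with no intervention effect, which could create or hide a benefit. Year eight has two supervised walking lessons a week and the controls have none, so willingness to be measured could differ by group, and allocation was not randomised.

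**Working it through.** **1. The effect implied by the stated sample size.** The 100:60 figure cannot be reproduced forwards because no effect size or SD is given. Solving backwards (two-sided 5% assumed, 80% power):

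d = (1.960 + 0.842) × √(1/100 + 1/60) = 2.802 × 0.1633 = 0.457.

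The noncentral t gives 0.460. A one-sided test would give 0.406.

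**2. Bias under selective refusal.** These settings are assumptions, not figures from the article: no true effect; standardised baseline; pre-post correlation r; the same proportion missing post in both groups; refusal unrelated to baseline in one group; and, in the other, odds of refusal multiplied by a fixed ratio (OR) per SD of baseline. Bias is in baseline SDs, for the group with selective refusal.

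| Missing, OR | Post values, r = 0.95 | Post values, r = 0.9 | Change, r = 0.95 | Change, r = 0.9 |
|---|---|---|---|---|
| 10%, 1.5 | −0.038 | −0.036 | +0.002 | +0.003 |
| 20%, 2 | −0.122 | −0.117 | +0.007 | +0.012 |
| 30%, 3 | −0.256 | −0.244 | +0.014 | +0.026 |

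Simulations at 100 v 60 and r = 0.95 gave the same post-value bias: 0.04, 0.12 and 0.26 SD. On change scores the bias is far smaller and of opposite sign. At r = 0.8 the change-score bias reaches 0.055 SD in the worst of these cells.

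**3. False positives on post values.** With standard error √(1/n₁ + 1/n₀) and λ = bias ÷ standard error, the rejection rate is about Φ(−1.96 + λ) + Φ(−1.96 − λ).

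- 10%, OR 1.5 (90 v 54): 0.038/0.172 = 0.22, giving 5.6%.
- 20%, OR 2 (80 v 48): 0.122/0.183 = 0.67, giving 10.3%.
- 30%, OR 3 (70 v 42): 0.256/0.195 = 1.31, giving 25.9%.

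Simulated rates were about 5–6%, 10–11% and 26–28%.

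**4. Size against the two available yardsticks.**

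- Implied d: 0.038/0.457 = 8%; 0.12/0.457 = 26%; 0.26/0.457 = 57%. To reach 0.457 SD, the heaviest 27% of one group would all have to skip, with no selective skipping in the other.
- Predicted 1.2 lb: 1.2 × 0.4536 = 0.54 kg. At an assumed body-mass SD of 10 kg, 10% missing with OR 2 (0.061 SD at r = 0.9) is 0.61 kg on post values, slightly more than the prediction; with OR 1.5 it is 0.36 kg, less than it. On change scores the OR 2 case gives 0.006 × 10 = 0.06 kg. For BMI at an assumed 1.55 m, 0.544/1.55² = 0.23 kg/m²; at an assumed SD of 4 kg/m², 0.12 SD is 0.48 kg/m².

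**5. Does using every baseline remove the bias?** The group × time likelihood estimate, which carries the baselines of children missing the post-test, had bias of about 0.001 SD or less in the same simulations. This is expected, because refusal was made to depend only on baseline.

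**6. Power.** If 20% are lost from 100 and 60, leaving 80 and 48: √(1/80 + 1/48) = 0.1826; 0.4575/0.1826 = 2.506; Φ(2.506 − 1.960) = 0.71.

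**The case against.** Several points on the other side are sound.

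- **Size.** A reader might infer that the bias is as large as the effect sought. The article states no effect sought. The 1.2 lb figure is an energy projection that the article itself qualifies as ignoring confounders, and it is not tied to the sample size. Against the effect implied by 100:60, the central case is about a quarter.
- **Which comparison.** The article does not commit to post values. If changes are compared, the problem nearly disappears when refusal depends only on baseline.
- **Differential refusal.** A reader might infer that refusal will differ between groups. Nothing in the article shows this. The stigma argument applies to both groups, and both are measured in PE lessons, by gender-specific staff, with confidentiality. Individual results come only after post-testing, which is a reason to attend.
- **Scope.** An article may leave the analysis set and missing-data rules to a fuller document, so their absence is not a fault. Voluntary measurement is an ethical condition, not a design error.
- **Power.** The numbers can fairly be read as those needed for analysis, in which case no power is lost.

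What survives is that the article does name its tests. Without imputation, a paired t-test excludes children lacking a value, and an independent t-test on post values makes no use of the baseline. That is a stated method, and it can be improved with data the study will already hold.

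**Conclusion.** The point holds as a conditional weakness of the named analysis. If the independent t-test compares post values, and if refusal depends on baseline weight or fitness in one group only, with 10–30% missing and odds ratios of 1.5–3 per SD, the bias is about 0.04–0.26 SD and false positives run from about 5% to 28%. That is roughly 8–57% of the implied d of about 0.46. It matches or exceeds the predicted 1.2 lb loss only for body mass or BMI on post values, and there only from about 10% missing with OR 2 upwards at the assumed SD of 10 kg. On change scores it is about 0.002–0.03 SD for correlations of 0.9–0.95. The missing rates, odds ratios, correlations and SDs are all assumptions. Refusal that depends on the change itself could do more harm, but the article gives no basis for sizing it. The fall in power to about 71% applies only if 100 and 60 are enrolled numbers and 20% are lost.

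**What to change.** In Data Analysis, replace the t-tests for the intervention effect with one repeated-measures mixed model containing group, time and group × time, fitted to every child with at least one measurement. The group × time term is the intervention effect, and the baselines of children who miss the post-test then contribute. This also settles whether post values or changes are compared.

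Report the number of missing post values for each measure, by group and by baseline status (for example baseline BMI and shuttle score). State that 100 and 60 are children with both measurements.

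The cost is a few sentences and modest extra programming, with no new data. The model assumes that refusal depends only on observed values, so it does not cure refusal driven by unobserved change. Nor does it address other consequences of allocating by school year.
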